#### Possible expected occurrences

In this study a number of potential occurrences are expected. Possible (expected) intraoperative occurrences associated with the intervention include anaesthetic related problems, intra-operative instrument failure, damage to adjacent organs and bleeding. Possible (expected) occurrences associated with either type of surgery occurring at any time during the trial include haemorrhage, requirement for blood transfusion, anal stenosis, anal fissure, pain, urinary retention, residual anal skin tags, anal fistula, prolapse, difficult defecation, faecal urgency, wound discharge, pelvic sepsis, systemic complications and pruritis.

Details of any of the occurrences listed above will be recorded on the case report forms and participant completed questionnaires and reported to the data monitoring committee (DMC).

#### Procedure for reporting untoward and related serious adverse events in this study

A serious adverse event (SAE) in the eTHoS trial is defined as when one of the following events occurs to a research participant:related (resulted from administration of any of the research procedures) andexpected or unexpected (that is, the type of event that is not listed above as an expected serious occurrence) that causes death, is life threatening, requires hospitalisation, results in significant incapacity/disability or is otherwise considered medically significant by the investigators.

All SAEs will be recorded on the Serious Adverse Event Report form. In addition, SAE forms will record all deaths due to any cause during the course of the study.

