## Background

### The burden of the problem

Haemorrhoids are common in all age groups from mid-teens onwards. In 2006 and 2007, approximately 25,000 haemorrhoidal procedures were performed in England as hospital day-case or inpatient admissions, resulting in significant calls on health service resources [1]. The treatment of haemorrhoidal disease is directed at relieving its related symptoms. Traditional surgical haemorrhoidectomy (TH) involves excision of the haemorrhoidal cushions and is generally advocated for symptomatic haemorrhoids of grade III or IV. This traditional approach, whilst effective, is however associated with severe pain.

Improved understanding of the pathogenesis of haemorrhoids [2], increasing belief in the importance of preserving the anal cushions and greater awareness of the complications associated with excisional haemorrhoidectomy led to the invention of newer surgical procedures including stapled haemorrhoidopexy.

Stapled haemorrhoidopexy (SH) was conceived over 15 years ago and was first described by Longo [Longo A: Treatment of haemorrhoidal disease by reduction of mucosa and haemorrhoidal prolapse with a circular suturing device: a new procedure, unpublished]. Its potential advantages over traditional surgery include a reduction of operating time, hospital stay, time to return to work and postoperative pain [3]. These features would seem to make it attractive to patients and healthcare providers. Nevertheless, uncertainties around complication rates, recurrence of symptoms and costs preclude its widespread use across the National Health Service (NHS).

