**The secondary objectives** are to compare sub-domains of health (SF-36 scores, pain and symptoms), disease recurrence, complication rates, and direct and indirect costs to the NHS, and cost-effectiveness (measured in terms of incremental cost per QALY, where QALYs are derived from responses to the EQ-5D).

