#### Safety

We will report serious adverse events in accordance with the guidance from the National Research Ethics Service (NRES), which is a subdivision of the National Patient Safety Agency.

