#### Secondary

The patient-reported outcomes include the following:generic health profile measured by SF-36 and EQ-5D,visual analogue scale (VAS) pain score,Cleveland incontinence score,haemorrhoid symptom score,post-operative analgesia consumption,recurrence of haemorrhoids, andtenesmus.

Clinical outcomes are perioperative and postoperative complications including the following:haemorrhage,requirement for blood transfusion,anal stenosis,anal fissure,urinary retention (which requires catheterisation),residual anal skin tags,difficult defecation,wound discharge,pelvic sepsis, andpruritus.

Economic outcomes will be the costs based on resource use data and include the following:Costs to the NHS and patients at two yearstime to recoverylength of hospital stayuse of health services for haemorrhoid related events or treatmentspatient costs (treatments, travel to health services, sick leave)need for alternative management for haemorrhoids (for example, surgery, drugs)other use of health servicesvisits to GP

ii. visits to practice nurse

iii. visits to colorectal surgeon2.Estimated lifetime cost to NHS and patient3.QALYs estimated from the EQ-5D at 24 months4.QALYs estimated over the patient’s lifetime5.Cost-effectiveness analysis (incremental cost per case of stapled haemorrhoidopexy and traditional haemorrhoidectomy excision avoided).

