##### Costs of intervention

The costs of the surgical interventions will be recorded on a per patient basis. The resources used to provide surgery will be calculated by consulting with relevant staff (surgeons, theatre nurses, business managers) and members of the trial team to elicit information on the following:reusable equipment,frequency of use of that equipment,consumables used during surgery,staff mix of the surgical team andoverheads costs for specific time periods.

In addition to this, the operative details will be collected on the CRFs and will provide estimates of the grade of operator, assistant and anesthetist, as well as relevant procedure times.

Unit costs for these resources will be based on nationally available data and study-specific estimates. Longer term estimates of resource use and cost will be derived from trial estimates and the literature.

Length of stay information will be elicited for each patient through the case report forms by collecting the date of admission and discharge. Unit costs for each level of care will be initially obtained from the Scottish Health Service Costs (SHSC) [15] for the primary analysis and NHS National Reference Costs in a secondary analysis. These sources will not have a cost per day for all hospital services; therefore some calculations will be needed to determine the ‘cost per day’ for each level of care.

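### The serious adverse event definition omits prolongation of the operative stay, so whether an in-hospital complication is serious rests on other criteria or on unblinded judgement

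*Protocol article*

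**What the plan says.** The protocol article prints its own SAE definition in the section on reporting untoward and related serious adverse events. The event must be related to a research procedure, may be expected or unexpected, and must be one that "causes death, is life threatening, requires hospitalisation, results in significant incapacity/disability or is otherwise considered medically significant by the investigators". Hospitalisation is the only criterion that concerns admission. Prolonging a stay already under way is not mentioned there or anywhere else in the article.

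Other sections bear on how this rule works:

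- Background, The burden of the problem, says of SH: "Its potential advantages over traditional surgery include a reduction of operating time, hospital stay, time to return to work and postoperative pain".
- Costs of intervention: "Length of stay information will be elicited for each patient through the case report forms by collecting the date of admission and discharge".
- Follow-up procedure and Measuring outcomes state that the surgeon and the participant know the allocated treatment.
- Reporting responsibilities of the chief investigator: the expedited report (15 days, or 7 for a related death) starts from a completed SAE form for a possibly related and unexpected event.
- Possible expected occurrences: "Details of any of the occurrences listed above will be recorded on the case report forms and participant completed questionnaires", with onward reporting to the data monitoring committee (DMC).
- Measures of outcome, Secondary: "Clinical outcomes are perioperative and postoperative complications including the following", followed by a list that carries no seriousness condition. The matching secondary objective names "disease recurrence, complication rates, and direct and indirect costs to the NHS". SAE frequency is not a listed outcome.

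**The concern.** Both treatments are operations done in hospital, so a complication can arise before or after discharge. After discharge, a complication that needs hospital care leads to an admission and meets the definition without further judgement. Before discharge, the usual consequence of the same complication is a longer stay, which the definition does not name. That event then counts only if it is life threatening, is incapacitating, or is "otherwise considered medically significant by the investigators". The last of these is discretionary, and those who apply it know the allocation.

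Two things are at stake. First, if one operation keeps patients in hospital longer, more of its early complications fall under the discretionary route, and the SAE tallies for the two arms are then not collected on equal terms. Second, a related and unexpected event that lengthens the stay but is not classed as serious does not start the expedited report. This second consequence does not depend on any difference between the arms.

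**Working it through.** The definition contains no figure to reproduce. The check is a comparison of sections, followed by an illustration on assumed inputs.

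**Step 1: one complication, two settings.** Take a related postoperative bleed that needs two days of hospital care.

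- After discharge the patient is readmitted. The hospitalisation criterion is met and the event is serious automatically.
- On the ward the patient is kept in for two more days. Prolongation is not listed, so the event is serious only through another criterion or the catch-all.

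**Step 2: direction.** A shorter stay is listed as a potential advantage of SH. If that holds, TH patients are more often still in hospital when an early complication occurs, so any under-count falls on TH.

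**Step 3: size, as an illustration only.** The article gives no complication rate and no day-case share by arm. Define:

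- r: true rate of related complications needing hospital care, equal in both arms. Assumed 6%.
- d: share of the arm treated as day cases, all of whose complications are taken to lead to an admission. Assumed.
- f: share of inpatients' complications that arise during the operative stay. Assumed 0.3 or 0.6.
- q: chance that another criterion or the catch-all captures such an in-stay event. Varied from 0 to 1.

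Recorded SAE rate = r × [d + (1 − d) × ((1 − f) + f × q)]. The ratio between arms does not depend on r.

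With d = 0.8 (SH) and 0.4 (TH), f = 0.6 and q = 0:

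- SH: 0.06 × [0.8 + 0.2 × 0.4] = 0.0528, or 21.1 per 400.
- TH: 0.06 × [0.4 + 0.6 × 0.4] = 0.0384, or 15.4 per 400.
- Ratio: 0.0528 / 0.0384 = 1.38.

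The 400 is the planned number per group. Other inputs give:

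| d, SH v TH | f | q | SAEs per 400, SH v TH | Ratio |
|---|---|---|---|---|
| 0.8 v 0.4 | 0.6 | 0 | 21.1 v 15.4 | 1.38 |
| 0.8 v 0.4 | 0.6 | 0.5 | 22.6 v 19.7 | 1.15 |
| 0.8 v 0.4 | 0.6 | 0.9 | 23.7 v 23.1 | 1.02 |
| 0.8 v 0.4 | 0.6 | 1 | 24.0 v 24.0 | 1.00 |
| 0.7 v 0.5 | 0.6 | 0 | 19.7 v 16.8 | 1.17 |
| 0.7 v 0.5 | 0.3 | 0 | 21.8 v 20.4 | 1.07 |
| 0.5 v 0.5 | 0.6 | 0 | 16.8 v 16.8 | 1.00 |

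The imbalance therefore needs both a difference in stay between the arms and incomplete use of the other criteria. Without either one the ratio is 1.00.

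**The case against.** A reader might infer that an in-stay complication is never serious under this rule, and that the trial's safety comparison is therefore biased. The documents support neither statement.

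- **The event is not excluded.** The catch-all, or the life-threatening or incapacity criteria, can make it serious. One could also read a complication that keeps a patient in as itself requiring hospitalisation. This objection stands: the classification is left to judgement, which is different from being ruled out.
- **The planned comparison does not use SAE counts.** It is of named complications whatever their seriousness. Haemorrhage, the bleed in the example above, is both a named outcome and a listed expected occurrence, so it is recorded and reaches the DMC in either setting. This also stands.
- **The Safety section defers to National Research Ethics Service guidance, and a fuller protocol exists.** Neither text is shown, and either might cover prolongation. That cannot be checked. The article nevertheless prints a full list of criteria as the trial's own definition, and a site following that list would find no such criterion.
- **The expedited route concerns only unexpected events, and the expected list is broad.** This makes the affected group small. Lead surgeons must also notify the study office of unexpected, possibly related events, but that duty carries no seriousness classification and no deadline.
- **The inputs on stay are weak.** The Background mentions day-case and inpatient care for national activity in England and gives no split for this trial. A shorter stay with SH is called a potential advantage. Minimisation on centre balances local discharge policy between arms, but would not remove a difference in stay caused by the operation itself. So the direction is a reasonable expectation and the size is unknown.

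**Conclusion.** The point holds in limited form. Followed as written, the definition makes SAE tallies, and entry to the expedited report, depend partly on whether the patient had gone home and partly on judgement by people who know the allocation. If SH does shorten the stay, the tallies could under-count TH relative to SH. The documents do not allow the amount to be estimated. In the illustration the ratio runs from 1.00, with equal day-case shares or full use of the catch-all, to 1.38 with a wide assumed difference in stay and no use of it. These ratios rest wholly on assumed inputs and are not predictions.

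The comparison of named complications and the DMC's view of listed occurrences are untouched. This is a gap in a definition, worth closing because it is cheap to close. It is not a demonstrated bias in the planned safety outcomes.

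**What to change.** In the SAE definition, extend the hospitalisation criterion so that it covers an event that either requires hospitalisation or prolongs existing hospitalisation. State beside it that the planned admission for the allocated operation is not itself an SAE. Put the same wording in the SAE form guidance.

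The Discussion reports more than 750 participants already randomised, so a new definition alone would leave most of the trial under the present wording. For those already operated on, use the admission and discharge dates and the complication items on the case report forms to find stays lengthened by a related complication, and complete SAE forms where the revised definition is met.

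The cost is a short protocol change, a look-back on data already collected, and a modest rise in the number of SAE forms.

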#### Reporting responsibilities of the chief investigator

When the web-based Serious Adverse Event form is completed detailing any possible related and unexpected SAEs, the chief investigator (CI) will be notified automatically. If, in the opinion of the local investigator and CI, the event is confirmed as being related and unexpected, the CI will submit a report to the main REC and the study sponsors within 15 days of the CI becoming aware of it or within 7 days if it is a death (related to the study).

### Measures of outcome

The study has a patient-centred and an economic primary outcome, and multiple secondary patient-reported, clinical and economic outcomes.

#### Primary

The patient-centred outcome is the quality of life profile over the follow-up period (area under the curve derived from EQ-5D measurements at baseline, 1 week, 3 weeks, 6 weeks, 12 months, EQ-5D at 18 months only if not completed at 12 months, 24 months and (subject to securing further funding) 60 months.

The trial economic outcome is the incremental cost per quality adjusted life year (QALY) gained with QALYs based on the responses to the EQ-5D at 24 months.

The economic model outcome is the incremental cost per QALY over the lifetime of the participant.

#### Secondary

The patient-reported outcomes include the following:generic health profile measured by SF-36 and EQ-5D,visual analogue scale (VAS) pain score,Cleveland incontinence score,haemorrhoid symptom score,post-operative analgesia consumption,recurrence of haemorrhoids, andtenesmus.

Clinical outcomes are perioperative and postoperative complications including the following:haemorrhage,requirement for blood transfusion,anal stenosis,anal fissure,urinary retention (which requires catheterisation),residual anal skin tags,difficult defecation,wound discharge,pelvic sepsis, andpruritus.

Economic outcomes will be the costs based on resource use data and include the following:Costs to the NHS and patients at two yearstime to recoverylength of hospital stayuse of health services for haemorrhoid related events or treatmentspatient costs (treatments, travel to health services, sick leave)need for alternative management for haemorrhoids (for example, surgery, drugs)other use of health servicesvisits to GP

ii. visits to practice nurse

iii. visits to colorectal surgeon2.Estimated lifetime cost to NHS and patient3.QALYs estimated from the EQ-5D at 24 months4.QALYs estimated over the patient’s lifetime5.Cost-effectiveness analysis (incremental cost per case of stapled haemorrhoidopexy and traditional haemorrhoidectomy excision avoided).

### Data collection and processing

Follow-up will consist of clinical follow-up at 6 weeks and postal questionnaires at 1 week, 3 weeks, 6 weeks, 12 months (and 18 months if EQ-5D not completed at 12 months), 24 months and (subject to securing further funding) 60 months, with the main outcome assessment planned once the 24-month (from the date of randomisation) follow-up is complete.

#### Measuring outcomes

In this study the colorectal surgeon and the participant will know which intervention the participant has received. Clinical outcomes will be collected by the ROs and the colorectal surgeons. CRFs can be obtained from the Trial Office by contacting [contact]. Table 1 shows the eTHoS schedule for physical assessment/data collection.

**Table 1 Tab1:** **eTHoS schedule for physical assessment/data collection**

	Baseline	Surgical form	1 week	3 weeks	6 weeks	12 months	18 months	24 months	27 months	60 months
Clinical status CRF or data	○				○					
Surgical details		○								
Patient preference	○									
6 weeks clinical follow-up					○					
EQ-5D	○		●∞	●∞	●∞	●∞	●∞	●∞		●∞
SF-36	○				●∞	●∞		●∞		●∞
Pain VAS			●∞	●∞	●∞					
Haemorrhoid symptom score	○				●∞	●∞		●∞		●∞
Cleveland incontinence score	○				●∞	●∞		●∞		●∞
Health care utilisation questions						●∞		●∞		●∞
Travel costs questionnaire									●∞	
Recurrence						●∞x		●∞		●∞x
Analgesia question			●∞	●∞	●∞					
DCE								∞ ●		
Hospital statistics for further surgery						●∞x				●∞x

○ Clinic; ● Postal; **x** HES, PEDW and ISD; ∞Web based. CRF, case report form; DCE, discrete choice experiment; EQ-5D, EuroQol Group’s 5 Dimension Health Status Questionnaire; SF-36, Short Form Health Survey 36 Question form; VAS, visual analogue score.

#### Patient reported outcomes

At baseline, (recruitment) participants will complete the patient reported outcome (PRO) questionnaires. In addition at 1 week, 3 weeks, 6 weeks, 12 months (EQ-5D only at 18 months if not completed at 12 months), 24 months and (subject to securing further funding) 60 months, participants will complete the eTHoS PRO questionnaires. These will be distributed by post and completed by the participant. Participants will be given the option to complete the 1-week, 3-week, 6-week, 12-month (EQ-5D only at 18 months if not completed at 12 months), 2-year and 5-year participant reported outcome questionnaires on a secure participant portal within the eTHoS website. Participants will be provided with a log-in to access the portal. In the event that these postal questionnaires are not returned, participants will be telephoned to obtain the missing data for the 1- and 3-week questionnaires. A postal reminder will be sent if there is no response to the 6-weeks, 12-month, 24-month and (subject to securing further funding) 60-month questionnaires. If they are not returned, a second reminder will be sent. If questionnaires are returned but not adequately completed, (that is, key outcome data are missing), either a member of the study office team or the RO, as appropriate, will telephone the participant and obtain the missing questionnaire data as required.

#### Healthcare utilisation

NHS costs for health services use in both secondary and primary care by the UK trial participants will be collected.

At 12, 24 and (subject to securing further funding) 60 months after randomisation, participants will provide information about their use of health services (via the health care utilisation questions within the eTHoS patient reported outcome instrument. A postal questionnaire survey of all participants will be used to ascribe costs to typical episodes of health service use (the Participant Travel Cost Questionnaire) sent approximately 27 months after randomisation. The underlying aim is to keep economic data collection as parsimonious as possible to minimise the burden on the participants and the effect on response rates.

#### Patient preference (baseline and discrete choice experiment)

Burch and colleagues [6] found that the two treatments differed in terms of short-term outcomes (earlier return to usual activities, pain) and differed in terms of the risk of recurrence. Quality of life measurement (and QALYs based upon them) may not fully represent patients’ preferences for treatments and their associated outcomes. Given this, global patient preference will be elicited at baseline using a single 5-point Likert scale response to a hypothetical example. Furthermore, a discrete choice experiment (DCE) to allow an in-depth elicitation of the individual strength of preference for the different treatments during the follow-up period will be conducted. The choice of attributes will relate to the trial outcome measures and reflect advice from members of the trial team, as well as evidence from the appropriate literature. One further attribute of the DCE will be patient cost, which will allow willingness to pay (WTP) to be estimated. In particular, willingness to pay for specific attributes of treatment will be assessed. Estimating willingness to pay from the DCE will enable these estimates to be combined into the broader economic evaluation. The DCE will also include an additional surgical intervention, haemorrhoidal artery ligation (HAL) to take into account all the treatment options available to patients with haemorrhoids.

The DCE will describe the intervention in terms of a number of characteristics (attributes), for example, time in short-term pain and risk of recurrence. The extent to which an individual values an intervention will depend upon the levels of these attributes [12, 13]. The DCE technique involves presenting choices to individuals that imply a trade-off in terms of the levels of the attributes. To define the attributes and levels for the DCE, a literature review will be conducted as well as taking expert advice on potential attributes from members of the research team. Once the attributes and levels are defined, experimental design techniques will be used to reduce the number of possible choice sets to a manageable size, whilst still being able to estimate utility scores. In addition to the choices derived from the experimental design, two choice sets will be added to test the internal consistency of responses. These will be dominant (better) choices for one option and respondents would be expected to choose them.

The questionnaire will be piloted amongst a small sample (members of the research group and Health Services Research Unit, Aberdeen) to refine all practical aspects of the survey and to ensure that respondents are making trade-offs between the attributes. Once the pilot is complete and the questionnaire refined, a proportion of trial participants (n =100) will be sent the DCE questionnaire. The questionnaire will be sent to an online survey panel of non-trial participants. Generalised linear (for example, logistic) regression models will be used to analyse the response data. The decision on which statistical model to use to analyse the data is an empirical one and will depend to a certain extent on the final data collected.

